**Figure 2 F2:**
[figure not shown]
Supervised exercises offered halfway through the intervention (week 4). The exercises of the sensor-based movement control group are displayed in the top row, the exercises of the static motor control group in the bottom row.

The home exercises consist of four exercises per week, that will be performed on non-therapy days. The non-supervised home exercises are listed in a workbook with text and pictures describing each exercise. In addition, a QR-code is added to each exercise linking to a video-instruction. These video-instructions will be available “unlisted” on YouTube. The therapists will encourage patients in their own manner to do their home exercises. Adherence to the home exercises will be measured by a questionnaire after the intervention and at follow-up at 26 and 52 weeks.

The full protocol of supervised sessions and home exercises is provided in Supplementary materials 2, 3.

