Movement control over less centrally located joints, such as the elbow or knee, can be trained using functional tasks, like bringing a spoon to the mouth or kicking a ball toward a pylon. The success of the execution (not spilling the soup or knocking over the pylon) can be used as an indication of good control over the movement of the joint. Providing meaningful feedback on spinal movements is more complicated. Sensors that measure spinal movements can offer a solution (14). There are several sensor-based training systems available on the market, but currently only a few randomized controlled trials incorporating these technologies have been published (15, 16). These sensor-based training systems can be used to offer accurate real-time feedback on spinal movements, which could help to improve spinal movement control. These systems provide the possibility to train spinal movement control relatively independent without the need of intensive supervision and/or a highly experienced therapist (17). Moreover, the training sessions are relatively easy to standardize and the progression from simple toward complex movements can easily be adapted to each patient's abilities and needs. The sensor-based exergames could be more engaging and motivating than conventional motor controlexercises, which might increase therapy adherence (18).

This paper describes the protocol for a randomized controlled trial to evaluate if a sensor-based movement control intervention enhances movement control of the spine in low back pain patients to a greater extent than a standard static motor control intervention. We will assess movement control using a custom made spinal movement controlled tracking task and a clinical test battery by Luomajoki et al. (19, 20). We hypothesize that a sensor-based movement control intervention will enhance movement control of the spine in low back pain patients measured by spinal movement controlled tracking tasks to a greater extent than a standard static motor control intervention. The majority of the tests in the clinical test battery by Luomajoki et al. (19, 20) involve no spinal movement, hence we hypothesize that the static motor control group will improve more on this outcome than the sensor-based movement control group.

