To confer clinical benefit beside movement control of the spine, we will also evaluate differences between the offered interventions in terms of therapy adherence, their respective effects on disability, pain intensity, fear avoidance beliefs, and health related quality of life.

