### Interventions

The Sensor-Based Movement Control and Static Motor Control intervention will be offered over a course of 8 weeks (weeks 2–9 of the study), each week consisting of two supervised therapy sessions of 20–30 min and four non-supervised home exercises of 5–10 min resulting in nearly one training session every day of the week for 8 weeks.

The supervised sessions are provided by five experienced (4–10 years) physio- and occupational therapists from the MRC that are trained to provide both the intended interventions. The therapists can also provide the regular therapies in the multidisciplinary rehabilitation programme of a patient. Three training moments are given to all therapists at the same time by the investigators to understand the content of the interventions and how to offer this to the patients during 8 weeks. The quality will be assured by several evaluation meetings with the investigators and investigators will check the content of the sessions by occasionally being present at the supervised sessions throughout the study. The first four sessions will be individual, i.e., one patient supervised by one therapist. In these sessions, the capacity of the patient will be determined by the therapists and the patient will get acquainted with the basics of the training. The final 12 sessions will be in groups, with a maximum of three patients in the same intervention per session, supervised by one therapist. The patients will not have the same therapist throughout the programme to keep the rehabilitation planning feasible. The therapists will monitor the progress and challenge the patient if needed during all sessions. There is a standard protocol for exercises throughout the sessions, for both the sensor-based movement control and static motor control group. This protocol was composed by two experienced physiotherapists/human movement scientists and are based on literature (6). Therapists are allowed to modify the standard exercises to match the difficulty level to the capacity of the patient. The standard exercises can also be deviated from to the need of the individual patient as long as it is within the scope of the assigned intervention. There is no standardized approach for modifications in progression, however all modifications will be registered. An example of the protocol for week four is presented in Figure 2. Attendance of the supervised sessions will be registered.

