#### Sensor-based movement control intervention

For the supervised therapy sessions of the Sensor-Based Movement Control intervention, Valedo^®^ Motion 2.0 (Hocoma) will be used. Valedo Motion is a medical device on which a patient can play games controlled with spinal movements. Spinal movements are tracked using three small inertial measurement units (IMUs), placed on the pelvis (S1), thorax (sternum) and thoracolumbar (L1) area of the spine. The orientation of these sensors is streamed to a laptop and used in real-time to control several games. These games are displayed on a laptop and invite the player to make controlled (in terms of movement direction, speed, and amplitude) movements of the spine in various postures (e.g., standing, sitting or on hands and knees). During the first few sessions, the workflow of the hardware and software will be demonstrated and explained by the therapist. It is expected that the patient can perform the set-up independently (under supervision of the therapist) after these two sessions. During each session, patients will play four different games. Before each session, the patients spinal range of motion around the three anatomical axes will be determined using the software. The standard protocol for games throughout the sessions are pre-set by the investigators and will be offered with increasing intensity, difficulty, and complexity. Modifications in progression of the patient will be registered by the treating therapist. The home exercises resemble the movements and postures of the Valedo games of that week. These exercises will also be adjusted to the capacity and need of the patient by the therapists, for example by changing the game duration or difficulty level of the game or by using exercise equipment.

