## Discussion

In this study, the effect of a sensor-based spinal movement control intervention on the movement control of the spine in low back pain patients over the course of a multidisciplinary rehabilitation programme will be compared to the effect of conventional static motor control exercises. In addition, we aim to evaluate the effect of the intervention on disability, pain intensity, fear avoidance beliefs and health related quality of life. Finally, therapy adherence will be compared between the interventions. Sensor-based exergames are a relatively new tool to train spinal movement control using meaningful and engaging feedback. To our acknowledge, this is the first study which evaluates if sensor-based exergames training influences movement control of the spine in low back pain patients to a greater extent than static motor control training.

Currently, there is no gold standard to assess movement control of the spine. Therefore, we will analyse our main outcome with three different assessments: [1] sensor-based tracking tasks on a laptop, based on a tracking task from Willigenburg et al. (12), [2] the clinical movement control test battery of Luomajoki et al. (19, 20) and [3] a self-developed clinical movement test battery. Because these tests are performed in the same subjects at the same moment, the results of this study could provide us more insight in how to assess movement control of the spine. The reliability and minimal detectable changes of the movement control tracking tasks and the self-developed clinical movement test battery are not available which may bias the outcome of the study.

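### Therapy adherence is to be compared between the interventions, but the one listed outcome (EARS) relates to the home exercises; attendance at the supervised sessions is registered but not named as an outcome

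*Protocol article*

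**What the plan says.** **Objective.** At the end of the Introduction the protocol article states that "we will also evaluate differences between the offered interventions in terms of therapy adherence", and the Discussion repeats that "therapy adherence will be compared between the interventions". The Introduction also explains why a difference might be expected: "The sensor-based exergames could be more engaging and motivating than conventional motor controlexercises, which might increase therapy adherence".

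**Measure.** Table 2 has one row for therapy adherence. It holds one instrument, EARS, marked at T1. The home-exercise paragraph under Interventions (after Figure 2) says: "Adherence to the home exercises will be measured by a questionnaire after the intervention". The Discussion links self-reported adherence to the same worry, compliance with home training.

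**Where the games are.** The section on the sensor-based intervention assigns Valedo Motion to the supervised sessions. For home training in both groups, "The non-supervised home exercises are listed in a workbook with text and pictures describing each exercise", with linked videos. For the sensor group, "The home exercises resemble the movements and postures of the Valedo games of that week".

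**Attendance.** The Interventions section says "Attendance of the supervised sessions will be registered". Attendance appears in neither Table 2 nor the list of secondary outcomes. The Statistical analysis section uses it once, to leave out of the analysis any patient who attended fewer than 10 sessions. Patients who drop out before T1 are left out as well.

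**The concern.** The objective concerns adherence to the interventions, and each intervention is a package of supervised sessions and home exercises. The listed outcome relates to the home part. The supervised part takes at least half of the planned time and is where the described game play takes place, yet it has no adherence outcome although the data will be collected.

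Two things are at stake. First, a result on home exercises would stand under the wider label of therapy adherence. A reader who has seen the engagement rationale could take a null EARS result as evidence against the exergames, or a positive one as direct evidence for them. Second, the 10-session rule is written for the statistical analysis without exception. If it also governs the adherence comparison, the patients who adhered least are removed first, and any difference between groups in how many stopped attending would not show.

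**Working it through.** The article gives no numerical figure for adherence, so there is none to reproduce. The check is dose arithmetic followed by a side-by-side reading.

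**Inputs (Interventions section).** Eight weeks; two supervised sessions a week of 20–30 min; four home exercises a week of 5–10 min.

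**Consistency of the inputs.** 2 × 8 = 16 supervised sessions, which matches the article's split into 4 individual and 12 group sessions. 4 × 8 = 32 home exercises. 2 + 4 = 6 training occasions a week agrees with the article's description of nearly daily training. This supports reading the 5–10 min as the length of each home exercise, which is the reading assumed here.

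**Planned time per patient.**
- Supervised: 16 × 20 = 320 min to 16 × 30 = 480 min; midpoint 16 × 25 = 400 min.
- Home: 32 × 5 = 160 min to 32 × 10 = 320 min; midpoint 32 × 7.5 = 240 min.

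**Share of planned time in home exercises** = home / (home + supervised).

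| Case | Calculation | Share |
|---|---|---|
| Shortest home, longest supervised | 160 / (160 + 480) | 25% |
| Both shortest | 160 / (160 + 320) | 33% |
| Midpoints | 240 / (240 + 400) | 37.5% |
| Both longest | 320 / (320 + 480) | 40% |
| Longest home, shortest supervised | 320 / (320 + 320) | 50% |

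The supervised part is the complement: 50–75% of planned time, 62.5% at midpoints.

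**Effect of the exclusion.** The cut-off is 10/16 = 62.5% of sessions. Attendance can run from 0 to 16 among allocated patients but only from 10 to 16 in the analysed set.

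**Side by side.**

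| Component | Content in the sensor group | Adherence data | Listed as outcome? |
|---|---|---|---|
| Supervised sessions | Valedo games | Attendance registered | No; used for the exclusion |
| Home exercises | Workbook and videos, resembling the games | Questionnaire (EARS) | Yes, Table 2 |

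Two links here are inferred. That EARS is the home-exercise questionnaire is not stated outright, but EARS is the only adherence instrument listed. That home training contains no games is likely from the workbook format and the word chosen for its likeness to the games, but it is not settled. The closing sentence of the sensor-based section mentions game duration and difficulty directly after the home exercises, and the full home programme is in supplementary material that is not shown.

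**The case against.** A reader might infer that the trial asks whether engaging exergames raise adherence and cannot answer that question. The document does not support this. The stated aim is a difference between the offered interventions. The engagement sentence is background in conditional terms, and the hypotheses in the Introduction concern only the tracking tasks and the clinical test battery. EARS answers the stated aim for home training. The home programmes differ between groups, and motivation carried over from supervised games would be part of that difference. It would therefore be wrong to say that EARS has no bearing on engagement. Nor should one say that it covers none of the game time, given the unclear sentence noted above.

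Further points on the other side are fair. Measuring home adherence is sensible, since unsupervised practice is otherwise unobserved. A condensed article may leave a summary of attendance by group to the full protocol or SAP, and nothing says that attendance will be used only for exclusion. The article nowhere says that EARS will be reported as adherence to exergames. The analysis is secondary and exploratory, and attendance in a scheduled rehabilitation programme may vary little.

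These points narrow the concern but do not remove it. The article does fix the adherence outcome, under a label wider than the component measured, and it fixes an exclusion on attendance with no exception for the adherence comparison.

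**Conclusion.** The concern holds in limited form. The adherence comparison as listed covers the component that makes up 25–50% of planned training time. It does not directly measure adherence to the supervised sessions, the other 50–75%. If the exclusion rule is applied as written, the comparison is also confined to patients who attended at least 10 of 16 sessions.

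This rests on EARS being the home-exercise questionnaire, on each home exercise lasting 5–10 min, and on Valedo being used in the supervised sessions as described. If the full protocol or SAP already compares attendance in all allocated patients, only the label of EARS and the patient set for its comparison remain to be settled.

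The conclusion should not be stretched to say that the adherence objective is unanswerable or that EARS is uninformative about motivation. The primary movement-control comparison is not affected by this point. The change is still worth making because it uses data already registered and serves the trial's own objective better.

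**What to change.** In Data collection and outcome measures (Table 2) and in Statistical analysis:

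1. Add the number of supervised sessions attended (0–16) as an adherence outcome alongside EARS.
2. Compare adherence between groups in all allocated patients with data, before the 10-session exclusion. For attendance this can include patients who drop out before T1.
3. Relabel EARS as adherence to home exercises and limit its conclusion to that component, without claiming that it has no bearing on engagement.

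While Table 2 is open, reconcile the timing: the home-exercise paragraph also plans the questionnaire at weeks 26 and 52, whereas Table 2 marks EARS at T1 only.

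The cost is one extra exploratory comparison on data already registered, a label change and a sentence on the analysis set. Attendance may lie near its ceiling and show little difference, so its distribution by group should be reported with the comparison.

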### Data collection and outcome measures

Patients will be tested at two instances, once before (T0: week 1) and once after the intervention (T1: week 10). In addition, we will contact them by email at 6- and 12-months follow-up (T2: week 26 & T3: week 52). Per follow-up moment, patients receive a maximum of 2 emails and 1 letter, to enhance completion of the follow-up. Table 2 highlights the measures collected at each point in time. At the start of the intervention study, patients' characteristics will be recorded to enable comparison of baseline characteristics of both groups.

**Table 2 T2:** Overview of outcome measurements in this study.

	**Intervention**		**Follow-up**	
	**T0**	**T1**	**T2**	**T3**
**Patient characteristics** Age, height, weight, BMI, gender, duration of complaints	X			
**Questionnaires** RAND-36, FABQ, NRS, ODQ, RMDQ	X	X	X	X
**Movement control assessment** Tracking tasks, clinical spinal movement control tasks, repetitive motion tasks and gait trials	X	X		
**Therapy adherence** EARS		X		

T0: week 1; T1: week 10; T2: week 26; T3: week 52.

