
We have no specific hypotheses regarding the aforementioned movement variability outcomes. These outcomes were primarily assessed as part of a case control study (see pre-registration https://osf.io/3dr58).

The tracking tasks, gait trials and repetitive motion tasks will be performed in quasi-random order at baseline and post-intervention measurements.

In addition to the movement control outcomes, patient reported outcome questionnaires will be assessed at baseline, post-intervention and at follow-up. The patient reported outcomes measured in this study will be: Exercise Adherence Rating Scale (EARS) (26), Dutch version of the Oswestry Disability Index (ODI) 2.1a (27), Dutch version of the Roland Morris Disability Questionnaire (RMDQ) (28, 29), three scores of Numeric Rating Scale (NRS) for Pain; the average and maximum pain intensity over the past 7 days and current pain intensity (29), Dutch version of Fear Avoidance Beliefs Questionnaire (FABQ) (30), Four scales of the Dutch version of the RAND-36 (Physical functioning, mental health, general health and pain) (31).

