### Statistical analysis

To evaluate if movement control of the spine changes differently between groups over the course of the treatment, repeated measures ANOVAs will be used to evaluate if a significant Group x Time interaction effect exists for the tracking error during each tracking task separately, the average tracking error of the tracking tasks and the total score of the clinical movement control test battery. The main effects of Group and Time will also be assessed using the same ANOVA. In addition to the total score of the clinical movement control test battery by Luomajoki et al. (19, 20) the performance on the individual tests that comprise the test battery will also be reported per group at T0 and T1.

Secondary study parameters will be assessed in the same manner as described above without correction for multiple testing, because these analyses are of an exploratory nature, and we want to limit the probability of type 2 errors. For the questionnaires that will be filled out on more than two occasions, we will perform *post-hoc* independent t-tests, with LSD correction, comparing results between groups at each point in time. Patient characteristics and all questionnaires filled out during the first testing day will be compared between groups using independent sample *t*-tests without correction for multiple testing to evaluate if differences existed at baseline. Statistical analyses in this study will not be adjusted for baseline differences between groups, as recommended by de Boer et al. (32). Independent of normality, parametric statistics will be used in this study and the alpha level will be set at 0.05 (33).

Data from patients who attended less than 10 sessions are not included in the statistical analysis. In addition, the data is also not included if patients have dropped out of the study before T1.

Missing data will be handled by using complete case analysis with all repeated measures ANOVAs between T0 and T1 and independent *t*-tests between T0, T1 and T2 and between To, T1, T2 and T3.

All statistical analyses will be performed using R version 4.1.1.

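### The text schedules home-exercise adherence at weeks 10, 26 and 52 but Table 2 schedules EARS at week 10 only, and the T0–T1 Group x Time ANOVA set for secondary outcomes fits neither schedule

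*Protocol article*

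**What the plan says.** Four places in the protocol article bear on adherence.

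- **Interventions, home-exercise paragraph after Figure 2:** "Adherence to the home exercises will be measured by a questionnaire after the intervention and at follow-up at 26 and 52 weeks". The instrument is not named there.
- **Data collection and outcome measures:** "Table 2 highlights the measures collected at each point in time". In that table the row "Therapy adherence EARS" has a single mark, at T1. The row "RAND-36, FABQ, NRS, ODQ, RMDQ" is marked at T0, T1, T2 and T3.
- **Secondary outcomes:** a collective sentence states that "patient reported outcome questionnaires will be assessed at baseline, post-intervention and at follow-up". The list that follows puts the adherence scale first: "The patient reported outcomes measured in this study will be: Exercise Adherence Rating Scale (EARS".
- **Statistical analysis:** for the primary outcome, "repeated measures ANOVAs will be used to evaluate if a significant Group x Time interaction effect exists". Then: "Secondary study parameters will be assessed in the same manner as described above without correction for multiple testing". Between-group t-tests at each time point are added for questionnaires completed at more than two visits. The missing-data paragraph places all the repeated measures ANOVAs between T0 and T1. Patients who attended fewer than 10 sessions, or who left before T1, are taken out of the statistical analysis.

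The Introduction and the Discussion both name adherence as something the trial will compare between the interventions. The Discussion also gives possible non-compliance with home exercises as the reason for measuring it.

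**The concern.** A schedule table is what trial staff usually work from. If the Interventions text is the intended schedule and staff follow Table 2, no adherence questionnaire goes out at weeks 26 and 52, and a report not requested at the time cannot be recovered later. If Table 2 is intended, the text promises follow-up data that will never exist.

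The analysis problem follows from the schedule. The method prescribed for secondary outcomes needs a baseline value. T0 is week 1 and the study exercises run in weeks 2 to 9, so no adherence to them can be reported at T0. An analyst holding the EARS data must therefore choose a method after the fact.

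The attendance exclusion adds a separate difficulty. The trial asks whether exergames improve adherence, and the analysis set first removes the patients who attended least. If more patients fall below the threshold in one arm than in the other, the comparison among those who remain would understate or hide that difference.

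**Working it through.** **Schedules side by side (adherence)**

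| Source | T0, week 1 | T1, week 10 | T2, week 26 | T3, week 52 |
|---|---|---|---|---|
| Interventions text | – | yes | yes | yes |
| Table 2, EARS row | – | yes | – | – |
| Secondary outcomes, collective sentence | yes, if read literally | yes | yes | yes |

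The first two rows conflict outright at T2 and T3. The third is a general sentence covering all the questionnaires and adds ambiguity: read literally, it asks for adherence before any study exercise has been done.

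**Does the prescribed ANOVA fit?** Interaction degrees of freedom = (groups − 1) × (time points − 1), with two groups.

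- T1 only (Table 2): (2 − 1) × (1 − 1) = 0. There is no interaction and no Time effect to test.
- T0 and T1 (the ANOVA as prescribed): (2 − 1) × (2 − 1) = 1. This needs a T0 value that neither Table 2 nor the Interventions text provides.
- T1, T2 and T3 (Interventions text): (2 − 1) × (3 − 1) = 2. This is computable, but it is not the T0–T1 ANOVA described.

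**Do the additional t-tests apply?** They require more than two completions. Under Table 2 there is one, so they do not apply. Under the Interventions text there are three, so they do.

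**Attendance exclusion.** Supervised sessions: 8 weeks × 2 = 16, which agrees with 4 individual + 12 group sessions. The threshold is 10/16 = 62.5% attendance. Patients below it leave the analysis set, and no exception is made for the adherence outcome.

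**The plan's own sample-size figure, to confirm that it is untouched.** For a two-group, two-time-point interaction with f = 0.25 and alpha = 0.05, the noncentrality is λ = f² × N × m / (1 − ρ). The article gives no correlation, so ρ = 0.5 is assumed. With N = 54 and m = 2, λ = 0.0625 × 54 × 2 / 0.5 = 13.5 on 1 and 52 degrees of freedom, and power is 0.9501. N = 52 gives 0.9424. The stated 54 is therefore reproduced under that assumption. It concerns movement control at T0 and T1, and EARS plays no part in it.

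**The case against.** The strongest case on the other side has four parts.

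**An analysis is available.** A reader might infer that no Group x Time test can be run on EARS, or that the adherence comparison has no valid analysis at all. The article does not support this. Under the Interventions schedule, an ANOVA over T1 to T3 can be computed and the between-group t-tests at each visit apply. Under Table 2, the article's main effect of Group would reduce to a simple two-group comparison at T1, and the Discussion makes clear that a comparison between the interventions is intended. What stands is narrower: the T0–T1 ANOVA as prescribed does not fit EARS under either schedule. This is more than detail left to an analysis plan, because the article fixes a method that does not suit the outcome.

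**There may be only two schedules.** The Secondary outcomes sentence introduces all the questionnaires together, and Table 2 deliberately gives EARS its own row. Treating that sentence as a firm third schedule would be too literal. That is accepted: it adds to the ambiguity, and the conflict proper is two-way. The Interventions text says only that a questionnaire is used, so identifying it with EARS is an inference, though no other adherence instrument is named.

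**Nothing may be lost.** A reader might infer that two of three adherence time points will be lost. That holds only if the Interventions text is the intended schedule. The intervention ends in week 9, so a single measurement in week 10 is a coherent choice, and the article does not settle which was meant.

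**The outcome is exploratory.** The secondary analyses are labelled so. That limits the weight of the point without removing the contradiction over what is collected.

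On the exclusion, attendance at supervised sessions is not the same thing as adherence to home exercises, and the article gives no figure linking them. Attendance is nevertheless part of adherence to the intervention, so filtering on it is hard to defend for this outcome.

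**Conclusion.** The point holds in limited form. The article contradicts itself on whether adherence is collected at weeks 26 and 52, and the broken-table explanation fails because the EARS row of Table 2 is intact. The T0–T1 ANOVA set for secondary outcomes cannot serve EARS, and the attendance exclusion conditions the adherence comparison on part of what it is meant to measure.

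The size is two of three visits in dispute for one secondary outcome, with 0 interaction degrees of freedom if Table 2 stands and 2 over T1–T3 if the Interventions text stands. The direction and amount of any bias from the exclusion cannot be worked out, because the article gives no expected attendance by arm.

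This rests on two assumptions: that the questionnaire in the Interventions text is EARS, and that no further document shown to staff already resolves the schedule. The primary analysis and the sample size are unaffected.

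**What to change.** 1. **Settle one EARS schedule** and make the Interventions text, Table 2 and the Secondary outcomes paragraph agree. If the Interventions text is intended, mark EARS at T2 and T3 in Table 2 and add it to the follow-up contacts already planned. If Table 2 is intended, correct the Interventions text. In either case, except EARS from the sentence that gives the questionnaires a baseline assessment.
2. **Exempt EARS from the T0–T1 repeated measures ANOVA.** State instead that the between-group difference in EARS will be reported with a 95% CI at each visit where it is collected.
3. **Use all allocated patients with EARS data** for this comparison, without the 10-session rule. Report how many per arm have no EARS score, and show registered session attendance by arm beside it.

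The cost is a few sentences and one table row. If follow-up collection is intended, it also adds one short questionnaire to contacts that already take place. Enrolment is under way, so the schedule should be settled promptly: any week-26 or week-52 contact that passes without the questionnaire is a permanent gap if those visits were meant.
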